#### Outcomes

The primary outcome of the study will be the absolute number of episodes of
RRT triggering in a timely manner, defined by any triggering that occurred
in the units randomized to the study and for which the patient had critheria
within a 24-hour window. Appropriate time will be considered if the RRT
appears at the bedside within 5 minutes after the yellow code is triggered
by a health professional. The triggering time as well as the arrival time
are recorded by the care team on a specific form attached to the patient’s
medical record.

The identification of whether the yellow codes were activated properly will
be verified by a care team not participating in the study. This verification
will be carried out by checking the codes identified by a specific platform
provided by the company *Eritel Telecomunicações
Ltda.* (Eritel Telecommunications Limited)
*versus* the codes recorded in the medical record. If the
platform originates a code, but it was not confirmed/effective according to
the nursing team’s verification, it will be considered false triggering
(improper triggering).

The following secondary outcomes will be considered: mortality rates, cardiac
arrest, need for ICU hospitalization (defined according to institutional
protocols and trained staff) and duration of hospitalization during the
study.

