#### Recruitment

The care team will be responsible for surveying all RRT triggering that
occurs in the randomized units. This survey is carried out using the
institution’s own printed form, as well as the collection of data recorded
on a platform provided by the company *Eritel
Telecomunicações Ltda*.

The information regarding triggering will be provided to IP-HCor for
registration and subsequent data collection from the medical records. In the
medical record, if any code generated by the platform is not identified, it
will be identified as a false triggering.

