#### Blinding

Considering the nature of the intervention, this will be an open-label study
in which the researchers, the care team and the patients will be aware of
the control or intervention clusters. During statistical analyses,
investigators and statisticians will be blinded to the study groups. To
avoid contamination between the groups as much as possible, the work
schedules of individual workers and the shifts of the nursing teams will
undergo the least possible change.

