#### Data management

Data collection will be carried out through electronic CRF in the Academic
REDCap environment. Data are entered directly into the data capture system
by team members from the coordinating center, as there is still no
communication between the Welch Allyn Connex^®^ Spot Monitor
(CSM)/Hillrom Connecta™ solution and the REDCap system. All episodes
of RRT triggering will be confirmed by the care team, as false RRT
triggering may occur unduly or accidentally during the study period. The
sponsor will support and maintain the devices and software throughout the
period of use in the clinical trial. All nurse staff from the intervention
group will be trained to trigger a RRT manually in case the system fails; in
this case, this activation will be registered and dealt with as an intention
to treat.

Data monitoring will be carried out by a data management team to collect
*missing* data and inconsistencies using R software. Once
all data are entered into the system and all discrepant or missing data are
resolved, the statistician team will review and lock the database for
further statistical analysis.

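### The plan names different deciders for whether a code is a proper activation, at least one of them unblinded, so exclusions as false triggering may differ by arm and bias the primary outcome in either direction

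*Protocol article*

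**What the plan says.** Four statements in the protocol article bear on whether a code counts.

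- **Outcomes:** whether codes were activated properly will "be verified by a care team not participating in the study", by comparing platform codes with the medical record.
- **Outcomes, same paragraph:** a platform code is excluded if it was not confirmed or effective according to "the nursing team’s verification, it will be considered false triggering".
- **Recruitment:** "The care team will be responsible for surveying all RRT triggering that" arises in the randomised units. A platform code with no counterpart in the medical record "will be identified as a false triggering".
- **Data management:** all episodes "of RRT triggering will be confirmed by the care team, as false RRT" activations can happen by accident.

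The Blinding section describes an open-label study "in which the researchers, the care team and the patients will be aware of" the cluster assignment. It promises blinding of investigators and statisticians during the statistical analyses. The Discussion adds that the team collecting and analysing the data will be blinded.

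**The concern.** The classification as proper or false decides which codes enter the primary outcome. The article assigns it to a team outside the study, to the nursing team and to the care team, without ranking them. Two people applying the article to the same records could therefore return different event sets.

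Blinding at data collection and analysis does not protect this step, because it acts on codes that have already been confirmed or disowned. At least the care team knows the arm when it confirms.

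The arms may also be exposed to different degrees. Under the Intervention section, the device system activates the response team automatically through the nurse call system, whereas in control wards a professional raises the code at the bedside. Unconfirmed codes could well be commoner in the device arm. If so, an unblinded and loosely assigned exclusion step acts more on one arm than on the other.

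**Working it through.** **Reading the statements together.** The most favourable reconciliation is that the outside team does the matching and takes the nurses' confirmation as its input. Under that reading a code the nurses do not confirm is still false, so the ward entry still decides. The article states no criterion for a confirmed or effective code and does not say that the verifier is blinded.

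**The plan's own figure.** Sample size calculation gives 70% v 88% timely, 90% power, 5% significance and 216 activations. With a two-sided test, pooled variance under the null and no continuity correction:

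n per arm = [1.96·√(2·0.79·0.21) + 1.2816·√(0.70·0.30 + 0.88·0.12)]² / 0.18² = 105.5, so 106 per arm and 212 in total. This is within 3% of 216 and is not disputed. It shows that the planning is on a proportion, as is the binomial model in Statistical analysis.

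**Illustration for the proportion.** Assumptions: 108 codes per arm (216/2), independent codes, 70% truly timely in both arms, and a share s of late codes labelled false in the device arm only. The shares are not in the article.

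- Timely device codes: 0.70 × 108 = 75.6. Late device codes: 0.30 × 108 = 32.4.
- Apparent timely proportion = 75.6 / (75.6 + 32.4(1 − s)) = 0.70 / (1 − 0.30s).
- Chance that a nominal two-sided 5% z-test favours the device = Φ{[d − 1.96·SE₀] / SE₁}. Here d is the apparent difference, and SE₀ and SE₁ are the pooled and unpooled standard errors with 108 control codes and 108(1 − 0.30s) device codes.

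| s | codes removed | apparent timely | difference from 70% | chance of favouring device |
|---|---|---|---|---|
| 0 | 0 | 70.0% | 0 | 2.5% |
| 10% | 3.2 | 72.2% | 2.2 points | 5% |
| 20% | 6.5 | 74.5% | 4.5 points | 11% |
| 30% | 9.7 | 76.9% | 6.9 points | 20% |
| 50% | 16.2 | 82.4% | 12.4 points | 53% |

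**The absolute count.** In every row the device arm still has 75.6 timely codes. On the outcome as worded in Outcomes, an absolute number of timely episodes, removing late codes changes nothing.

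**The other direction.** Suppose the device truly reaches 88%. It then has 0.88 × 108 = 95.0 timely codes against 75.6 in control. Labelling 20% of its timely codes false leaves 95.04 × 0.80 = 76.0, and the advantage in count is gone. The proportion falls too, to 76.03 / (76.03 + 12.96) = 85.4%.

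**The case against.** The statements can be read as one workflow: ward staff record the code and its times, an outside team checks the platform against the record, and an unconfirmed or unmatched code is false. Data management's care team might even be the non-participating one. The full protocol, which is not shown, may set out the roles. This softens the contradiction but does not remove it, because the article speaks to the point and gives different answers, and on the single-workflow reading the ward entry still decides.

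Other parts of the objection stand and limit the point.

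- A reader might infer that ward staff would discard late device codes to favour the device. The documents do not support this. Lateness is the response team's arrival at the bedside, not an action of the ward nurses, and nothing says that the response team verifies codes. A late code with a completed form would normally match the record.
- A reader might infer that only device codes can be removed. Recruitment applies the form, the platform and the false-triggering rule to all randomised units, and Data management names no arm.
- A reader might take the 12.4-point gain as the expected bias. It needs half of all late device codes to be discarded and no others; no document gives any such share.
- Ward confirmation cannot simply be dropped. An outside team working from records could not otherwise recognise an accidental code.

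The Discussion already calls the trial exploratory and names performance bias as a limitation, but it does not address who verifies codes.

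**Conclusion.** The conflict over who decides is in the text, and it affects which events enter the primary outcome. At least one named decider knows the allocation, and the stated blinding comes after the decision. A difference between arms in exclusions is plausible because codes arise differently, but it is an inference.

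Neither the size nor the direction of any bias can be read from the article. For the proportion, and only under removal of late device codes with independent codes and 70% truly timely in both arms, shares of 10% to 50% give an apparent 72.2% to 82.4% and a nominal test favouring the device about 5% to 53% of the time. For the absolute count, the same removals have no effect, and removing timely codes works against the device. The point is worth correcting on those terms; it does not show that the trial would favour the device.

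**What to change.** Reconcile Outcomes, Recruitment and Data management so that:

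1. The non-participating team already named in Outcomes makes the final classification of every platform code in both arms, by one written criterion.
2. Arm and response time are masked for that team as far as the records allow, and ward-staff confirmation is kept as an input, not as the decision.
3. All platform codes, and the number classed as false, are reported by arm.
4. A sensitivity analysis of the primary outcome keeps the excluded codes.

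This is still possible at the stage the article describes: recruitment ended in September 2021, but properly triggered activations are still being identified. Bedside confirmations already made cannot be redone under masking; the later classification and the reporting can still change. The cost is the preparation of masked extracts, which takes some effort because codes must be matched to physical records, and one extra analysis. No new patient data are needed.

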#### Timeline

All RRT activations that occur in randomized units (intervention and control)
will be recorded until the necessary number estimated in the sample
calculation is obtained. The medical records of the respective patients will
be obtained for evaluation and recording of data referring to primary and
secondary outcomes (Figure 2). The
general protocol schedule is described in table 1.

**Table 1 t1:** General study schedule

	Study period			
	**Prerecruitment**	**Recruitment**	**Post-recruitment**	**Close-out**
Timepoint	November 2019 - March 2021	April - September 2021	October 2021 - March 2022	April - August 2022
Study design	X			
Submission and approval of the study protocol by the REC	X			
Team training	X			
Recruitment - Intervention group and control group		X		
Input of all data in the database (REDCap system)			X	
Data analysis				X
Submission of results				X

**Figure 2 f2:**
[figure not shown]
Study flowchart.

#### Sample size calculation

A set of three wards with 28 beds will be considered the intervention cluster
(with the Welch Allyn Connex^®^ Spot Monitor (CSM)/Hillrom
Connecta™ solution), and a set of three wards with 28 beds will be
considered the control cluster. The average monthly number of episodes of
RRT triggering in the six selected wards is 12, of which it is estimated
that approximately 70% are triggered in a timely manner. For an absolute
increase of 18% in the proportion of timely RRT triggering (88%) in the
intervention group, with a test power of 90% and a significance level of 5%,
we estimated a sample size of 216 RRT activations.

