**Methods:**

The Hillrom study is a single-center, open-label, superiority,
cluster-randomized, parallel-group (1:1 allocation ratio) clinical trial
that will be conducted in a tertiary hospital. Two sets of three wards with
28 beds will be included (one as the intervention cluster and the other as
the control). The wards will be randomly assigned to use the Welch Allyn
Connex^®^ Spot Monitor/Hillrom Connecta™
automated solution (intervention cluster) or to maintain the usual routine
(control cluster) regarding rapid response team activation. The primary
outcome will be the absolute number of episodes of rapid response team
triggering in an appropriate time; as secondary outcomes, clinical features
(mortality, cardiac arrest, need for intensive care unit admission and
duration of hospitalization) will be assessed according to clusters in an
exploratory way. A sample size of 216 rapid response team activations was
estimated to identify a possible difference between the groups. The protocol
has been approved by the institutional Research Ethics Committee.

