### Eligibility criteria

The inclusion criteria used to define the inpatient units (clusters) of the study
will be availability as defined by the heads of the hospital’s nursing area.
Patients admitted to the selected wards (all must be of medium complexity) who
triggered the RRT during the recruitment period will be included in the study;
patients with indications for blood pressure measurement via the lower limbs
(ankle) and those who are not candidates for either resuscitation or organ
support in the ICU will be excluded.

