#### Allocation

The allocation of the selected wards to the intervention or control groups
will be performed randomly and stratified by blocks according to the size of
the cluster through the *sample* function of R 4.0.2 software
(R Core Team, Vienna, Austria, 2020). Only the IP-HCor statistician team
will have access to the allocation list.

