#### Statistical analysis

The demographic and clinical characteristics of the sample will be summarized
according to the groups in absolute and relative frequencies for the
categorical variables; continuous variables will be presented by position
statistics (mean, median) and scale (standard deviation and interquartile
ranges).

The analysis for the primary outcome (events that trigger the RRT in a timely
manner) will be conducted with a logistic regression model considering
binomial distribution from generalized estimation equations, considering a
uniform work correlation matrix between patients of the same ward adjusted
for the baseline number of episodes of RRT triggering in an appropriate
timely manner. Other outcomes will be compared using a similar methodology
considering the response distribution that best fits the data. All results
will be presented considering measures of effect with respective 95%
confidence intervals.

Sensitivity analyses for the primary outcome considering time series
assessments and time of RRT activation (weekday *versus*
weekend; night *versus* day shifts) will be performed
comparing treatment groups. The results will be presented in graphs with
monthly indicators.

It is not expected that there will be a large amount of missing data.
However, if some of the primary and secondary outcomes are missing, the
missing data rate will be reported by group, and the values will be imputed
by chained equation multiple imputation methods using the mice package with
sample base characteristics.

All analyses will be performed with statistical R software 4.0.2 (R Core
Team, Vienna, Austria, 2020). Interim analyses or the participation of a
Data and Safety Monitoring Committee (DSMC) are not foreseen in the
protocol.

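### The protocol names both a three-ward set and the single ward as the cluster; the ward is the likelier unit, but then the primary interval rests on only six clusters

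*Protocol article*

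**What the plan says.** Two places define the cluster as a set of wards. The Sample size calculation section states "A set of three wards with 28 beds will be considered the intervention cluster" and describes the control cluster in the same way. The abstract's Methods paragraph, speaking of the two sets, has "28 beds will be included (one as the intervention cluster and the other as" the control.

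Other places make the single ward the unit:

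- Abstract, Methods, next sentence: "The wards will be randomly assigned to use the Welch Allyn" solution or to keep the usual routine.
- Study setting: wards are selected and then randomly assigned.
- Eligibility criteria: "The inclusion criteria used to define the inpatient units (clusters) of the study" equates the inpatient unit with the cluster.
- Allocation: "The allocation of the selected wards to the intervention or control groups" is what is randomised, and it "will be performed randomly and stratified by blocks according to the size of" the cluster.
- Statistical analysis: the primary GEE has a "uniform work correlation matrix between patients of the same ward adjusted" for the baseline number of timely episodes.

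The number of wards is six ("RRT triggering in the six selected wards is 12, of which it is estimated"). The abstract and the Trial design section call the trial a superiority trial, and the Statistical analysis section promises effect estimates with 95% confidence intervals.

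**The concern.** In a cluster-randomised trial, the number of allocated units fixes how much information there is about between-unit variation, and so whether and how an interval for the intervention effect can be formed. The article gives two answers: two units or six.

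With two units, any lasting difference between the two groups of wards (staffing, case mix, distance from the response team) cannot be separated from the device effect. With six units, a comparison is possible, but it rests on three wards per arm, and large-sample GEE intervals are not reliable with so few clusters. In both cases the strength of a superiority statement depends on a design fact that the article does not settle.

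**Working it through.** **1. Does the sample size reveal the unit?** Inputs from the Sample size calculation section: 70% versus 88% timely, power 90%, significance level 5% (taken as two-sided), 1:1 allocation. With pooled variance in both terms, the mean proportion is 0.79 and

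n per arm = (1.960 + 1.282)² × 2 × 0.79 × 0.21 / 0.18² = 10.507 × 0.3318 / 0.0324 = 107.6, rounded up to 108, so 216 in total.

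The stated 216 is reproduced by a formula for independent activations. It contains no allowance for clusters of either kind and so does not show which unit was meant.

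**2. Do the sections agree?** They do not.

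| Place | Unit |
|---|---|
| Abstract, Methods (sentence on the two sets) | Set: one per arm |
| Sample size calculation | Set: one per arm |
| Abstract, Methods (next sentence) | Ward |
| Study setting | Ward |
| Eligibility criteria | Inpatient unit, i.e. ward |
| Allocation | Ward, stratified by cluster size |
| Statistical analysis | Ward (working correlation) |

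Stratifying by cluster size has no function when only two units exist and both are described alike. This favours the ward.

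**3. If wards were allocated.** There are six clusters, three per arm.

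- Degrees of freedom for between-ward variation without a covariate: 6 − 2 = 4. The two-sided 5% critical value is t = 2.78.
- Error when 1.96 is used instead: 2 × P(T₄ > 1.96) = 0.122, about 12%.
- If the baseline count enters as one value per ward, it costs one more degree of freedom: 6 − 3 = 3, with critical value 3.18.
- Relative to 1.96, the interval widens by 2.78 / 1.96 = 1.42 (4 degrees of freedom) or 3.18 / 1.96 = 1.62 (3 degrees of freedom), for the same standard error.
- Without stratification there are C(6,3) = 20 possible allocations, so the smallest two-sided randomisation p-value is 2/20 = 0.10.

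**4. If sets were allocated.** There are two units, and 2 − 2 = 0 degrees of freedom for between-set variation. Only two allocations are possible, so the smallest two-sided randomisation p-value is 2/2 = 1.0. The ward-level GEE would still print a p-value, but its error term comes from variation among wards and omits variation between sets. It would be valid only if sets did not differ beyond their wards, which this design cannot check. Adjusting for baseline counts does not restore the missing degrees of freedom.

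**The case against.** The strongest reply is that the set wording is loose and the operative text is clear. The Allocation section, where the unit ought to be stated, randomises wards and stratifies them by size. The Blinding section uses the word cluster as a label for the arms, and the abstract's glosses can be read the same way. The Sample size calculation section says how the sets are regarded, not that sets were drawn. Most of this stands, and it is why the ward is the likelier reading. It remains an inference, because no sentence says that cluster means arm in those places. The study flowchart is not shown and might settle it, but the text would still conflict.

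A second reply is that the Discussion already concedes an unknown intraclass correlation, a small sample and an exploratory study. That softens any claim from the trial. It does not mention the unit or the number of clusters per arm, and the superiority label remains.

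A third reply is that the small-sample reference may be in an analysis plan that is not shown. That is fair, so the 12% is conditional on a normal reference being used. Which unit was allocated is a design fact, and the article itself states it inconsistently.

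A reader might go further and infer that the trial has no valid test at all, or that its type I error lies between 17% and 44%. The documents support neither. The first follows only if sets were allocated, which the Allocation section speaks against. The second comes from treating 108 activations per set as independent under an assumed intraclass correlation of 0.01 to 0.05. The planned GEE does not ignore clustering, the article gives no such correlation, and the calculation also assumes that activations in different wards of a set are as alike as those within one ward.

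**Conclusion.** The inconsistency is real and unresolved in the text; the ward is the more probable unit. On that reading the trial can support an interval, but from six clusters. A normal reference would carry about 12% type I error in place of 5%, and the correct critical value is 2.78, or 3.18 with a ward-level baseline covariate.

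The 12% assumes a standard error that behaves like an ordinary between-ward estimate from six roughly equal wards. It needs no intraclass correlation, and it is not a simulation of the planned GEE. The choice between 4 and 3 degrees of freedom depends on whether the baseline count is one value per ward. The Discussion's reference to baseline values in the participating wards suggests that it is, but the article does not say so outright.

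On the less likely set reading there is one unit per arm, and no between-set error to support a superiority test.

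**What to change.** State in the abstract, the Sample size calculation section and the Allocation section which unit was actually allocated, and use the word cluster for that unit only. Recruitment is complete, so this reports a known fact and changes nothing in the conduct.

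- **If the ward:** say that there are six clusters, three per arm. Base the primary interval on ward-level variation, with a small-sample method and a t reference: 4 degrees of freedom unadjusted (critical value 2.78), or 3 (critical value 3.18) if the baseline count is a ward-level covariate. Say which applies.
- **If the set:** say so, and present the comparison between arms descriptively, without a superiority test.

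The cost is a few sentences and a choice of reference distribution, made before the analysis. The downside is a wider stated interval, by a factor of about 1.4 to 1.6 relative to a normal reference if wards were allocated, and no formal superiority claim if sets were.

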## METHODS

### Study setting

The study will be conducted in a tertiary hospital located in the Southeast
region of Brazil. The HCor Research Institute (IP-HCor) will be responsible for
the protocol and coordination of the study. Data collection will commence after
compliance with all regulatory requirements, as well as training and adjustments
to the platforms and communication network necessary for automatic activation of
the RRT. There is no predetermined time for conducting the study; the admissions
of patients to the inpatient units will determine the study length. Wards with a
similar patient profile and a higher number of RRT activations compared to
regular wards will be selected and randomly assigned to use the Welch Allyn
Connex^®^ Spot Monitor (CSM)/Hillrom Connecta™
solution (Figure 1) or to maintain their
usual routine.

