trial, the effectiveness of an automated vital signs monitoring system
associated with the automatic activation of the RRT on the absolute number
of triggers in an appropriate timely manner. Additionally, we will assess
clinical outcomes (mortality, cardiac arrest, need for ICU hospitalization
and duration of hospitalization) in an exploratory manner according to the
study groups. The assessment of RR manually is a limitation of this study,
considering that it is usually the least documented vital sign strongly
related to measurement errors;^(25)^ in this sense, the number of RRT activations might
be impaired. The unicentric characteristics and the small sample size are
other limitations of this protocol. Considering that we had no knowledge of
the intraclass correlation coefficient to make the appropriate formal
calculation for the cluster design, the sample size calculation was only a
preliminary estimate, characterizing this study as exploratory; on the other
hand, statistical analyses should adjust for the baseline values of RRTs in
the participating wards, which should reduce the random error of the
estimates. Additionally, the selection of the primary outcome was made
taking into account the exploratory design of this trial. We hope that from
the results obtained, it will be possible to carry out a multicenter study
with greater coverage so that we can confirm our findings. Another potential
limitation is performance bias, since it is an open-label study because of
the nature of the intervention. However, all other procedures involving the
management of patients in the wards will be maintained at the discretion of
the medical and nursing teams involved in the assistance. In addition, we
chose objective outcomes, and the team performing data collection and
statistical analysis will be blinded to the participant’s group, minimizing
the effects of this potential bias on the results.

The recruitment of the study was completed in September 2021. Currently, the
Hillrom study is in the data collection phase, identifying RRTs that have
been properly triggered. The study is expected to end in August 2022.

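### The stated activation rate, the target of 216 activations and the April to September 2021 recruitment period do not fit together

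*Protocol article*

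**What the plan says.** All the relevant statements are in the protocol article.

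- **Rate** (Sample size calculation): the monthly average is given as "RRT triggering in the six selected wards is 12, of which it is estimated". On its face, 12 is the total for all six wards. The timely share in current practice is put at about 70%.
- **Target** (same section): the design assumes a rise from 70% to 88% timely, 90% power and a 5% level. The result reads: "we estimated a sample size of 216 RRT activations".
- **Calendar** (Timeline, Table 1): the recruitment column reads "April - September 2021", which is six months.
- **Stopping rule** (Timeline, text): activations in the randomized units are recorded until the calculated number is reached. Study setting agrees: "There is no predetermined time for conducting the study".
- **Status** (Discussion and trial status): "The recruitment of the study was completed in September 2021". The article does not say how many activations had accrued by then.

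**The concern.** A planned rate multiplied by a planned duration should come close to the planned number. Here it gives a third of it on the literal wording, and nothing in the article explains the gap. At least one of three things is therefore misstated or unexplained: the unit of the rate, the calendar, or the number on which recruitment closed.

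It matters which one. If the calendar closed recruitment and the literal rate is right, the comparison has about half the power a reader will attribute to it, and a null result would be read as coming from a trial with 90% power. If the rate is misprinted, the power statement is untouched by accrual, but the larger multicentre study that the authors hope will follow would inherit a planning rate that is too low by a factor of two or six.

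**Working it through.** **Inputs.** From Sample size calculation: rate 12 a month, control proportion 0.70, intervention proportion 0.88, power 90%, significance level 5%, target 216. From Table 1: six months. From Discussion and trial status: the cited before-and-after study, with activations rising from 405 to 524. Assumptions: a two-sided test (the article does not say), equal numbers of activations per arm (the 1:1 ratio applies to wards), and independent activations.

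**Step 1. Reproduce the target.** With pooled null variance, the mean proportion is (0.70 + 0.88)/2 = 0.79.

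- Null term: √(2 × 0.79 × 0.21) = 0.5760
- Alternative term: √(0.70 × 0.30 + 0.88 × 0.12) = 0.5618
- n per arm = (1.960 × 0.5760 + 1.2816 × 0.5618)² / 0.18² = 105.5, rounded up to 106, or 212 in total

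This is within 2% of 216, and power at 108 per arm is 90.7%. So 216 is a sound figure for an individual-level comparison, and the difficulty lies in the rate and the calendar.

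**Step 2. Accrual under each reading of 12.** Six-month count = monthly total × 6. Power = Φ[(0.18 × √n − 1.960 × 0.5760) / 0.5618], with n per arm.

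| Unit of 12 | Monthly total | Six-month count | Months to reach 216 | Power at six-month count |
|---|---|---|---|---|
| All six wards (literal) | 12 | 72 | 18 | 46.5% (n = 36) |
| Each three-ward set | 24 | 144 | 9 | 76.1% (n = 72) |
| Each ward | 72 | 432 | 3 | 90.7% if stopped at 216 |

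For the literal row: (0.18 × 6 − 1.129) / 0.5618 = −0.087, and Φ(−0.087) = 0.465. A one-sided test would give 59%. At 36 per arm, 90% power against 70% would require about 97% timely in the intervention arm instead of 88%.

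**Step 3. Can chance or the intervention close the gap on the literal reading?**

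- Chance: a Poisson count with mean 72 has a 95% range of about 56 to 89.
- Intervention effect: applying 524/405 = 1.294 to the intervention wards gives 36 + 36 × 1.294 = 83.
- Rise needed: with control wards unchanged at 36, the intervention wards would have to supply 216 − 36 = 180, and 180/36 is a fivefold rise.

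Exclusions and unconfirmed triggers can only lower the usable count.

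**Step 4. What rate would match?** 216/6 = 36 a month, which is none of the three readings. On the per-ward reading, 216 usable activations would take the full six months only if half of the 432 were ineligible or unconfirmed.

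**The case against.** The strongest reply is that the plan is driven by a count. Study setting and Timeline both let the number of activations decide the length, so accrual need not average 36 a month; it need only reach 216 before recruitment closes. If 12 is an average per ward, it does so in about three months, since 12 × 6 × 3 = 216. That reading is not far-fetched: the wards were to be chosen for having more activations than regular wards, and a total of 12 is only two per ward per month. Exclusions, false triggers and a delayed start could then account for a longer window.

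Much of this stands. The 90% is attached to 216 activations and not to six months, so it is correct as a planning figure. An open-ended plan and a September 2021 close do not contradict each other, because a trial that stops on a count still ends on some date.

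What does not stand is that this removes the inconsistency. The printed sentence gives 12 for the six wards and does not say per ward. If per ward was meant, the sentence is wrong by a factor of six. The article's description of the study as exploratory does not help either: that caveat concerns the unknown intraclass correlation, and the mention of a small sample does not address accrual against 216.

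**Conclusion.** The rate, the target and the recruitment period are mutually inconsistent as written. On the literal wording the six months yield about 72 activations, a third of 216, with power of about 47%. On the per-set reading they yield 144, with about 76%. On the per-ward reading 216 is attainable in about three months and the fault is in the printed rate. The power figures assume a two-sided 5% test, equal arms and independent activations.

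A reader might go further and infer that the trial stopped at a third of its planned information, or that 90% power was out of reach. The documents do not support that: the unit of the rate is open to question, no section says the calendar overrode the count, and the status paragraph does not say the target was missed. Nor should a further loss of power from clustering be charged to this point. It would depend on an intraclass correlation that the article says was unknown, and it is a separate limitation that the authors acknowledge.

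The inconsistency should be corrected because it bears on the size and power claimed for the primary outcome.

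**What to change.** 1. In Sample size calculation, state whether 12 is the monthly total for all six wards, for each three-ward set or for each ward, and correct the sentence if it is not the first.
2. In Timeline or the trial status paragraph, state whether reaching 216 activations or the end of September 2021 closed recruitment.
3. Report the number of eligible, confirmed activations accrued, by arm.
4. If that number is below 216, restate the power or the detectable difference for it, and present 90% only as the planning figure for 216 independent activations.

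This costs a few sentences and at most one recalculation, with no further enrolment. The possible downside is a less favourable stated power.
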